## Abstract

**Background:**

According to the World Health Organization’s infant and young child feeding guidelines, infants should be exclusively breastfed for the first 6 months of life. Despite public health campaigns to increase exclusive breastfeeding (EBF) rates, socioeconomic inequities persist among low-income breastfeeding mothers, especially in countries with large wealth and health gaps, such as Brazil. Social transfer programs are initiatives that provide financial support to individuals or households to improve their well-being and reduce financial burdens. These may be conditional, requiring recipients to meet specific criteria to receive the transfer, or unconditional, in which recipients receive the transfer without prerequisites. Evidence suggests that conditional and unconditional social transfers may help increase EBF rates while addressing the economic challenges breastfeeding mothers face. A randomized controlled trial (RCT) conducted in Vientiane, Lao People’s Democratic Republic, found that a social transfer program significantly improved both EBF rates at 6 months and EBF duration. Building on this study, we aim to evaluate the impact of this intervention in a different socioeconomic and cultural context.

**Objective:**

This protocol aims to implement an RCT to assess whether conditional and unconditional social transfers improve EBF rates at 6 months postpartum for mothers in low-income communities in São Paulo, Brazil.

**Methods:**

A prospective RCT will be conducted among 400 mothers who gave birth in the last 72 hours and plan to exclusively breastfeed. Participants will be recruited in São Paulo at the University Hospital of São Paulo and Amparo Maternal. Participants will be randomly assigned to one of the following groups: (1) control group—no social transfer; (2) intervention group 1—an unconditional social transfer at 6 months postpartum; and (3) intervention group 2—a social transfer at 6 months postpartum, conditional upon mothers’ EBF. All groups will receive educational materials supporting EBF. The study will have visits at birth, 1 month, 6 months, 1 year, and 2 years and will include a questionnaire and biological collections of breast milk samples, infant fecal samples, and blood samples (finger pricks) from both the mother and infant. The main study outcomes are the prevalence of EBF at 6 months and the duration of EBF across the 3 groups, where we hypothesize higher rates of EBF among mothers in the conditional group.

**Results:**

Recruitment began on March 6, 2024. As of September 2025, we enrolled 204 participants. Our goal is to recruit 400 mother-infant dyads by October 2025, with study visits expected to be completed by October 2027.

**Conclusions:**

We hypothesize that the Social Transfers for Exclusive Breastfeeding in Brazil (STEBB) intervention will positively impact breastfeeding mothers in São Paulo. If successful, the program may inform national policy to enhance Brazil’s existing social transfer program for new mothers.

**Trial Registration:**

ClinicalTrials.gov NCT06157697; https://clinicaltrials.gov/study/NCT06157697

**International Registered Report Identifier (IRRID):**

DERR1-10.2196/75796

## Introduction

### Background

Breastfeeding is one of the most cost-effective ways to improve health and development outcomes for infants [1]. The World Health Organization (WHO) recommends that infants be exclusively breastfed for the first 6 months of life [2]. Exclusive breastfeeding (EBF) is defined as infants receiving only breast milk, with no other liquids or solids given, with the exception of oral rehydration solution, vitamins, minerals, or medicines [2]. Infants who are exclusively breastfed for a longer duration have strengthened immune systems, lower rates of infectious diseases, improved cognitive development, and overall lower mortality rates [3-9]. Mothers who exclusively breastfeed have improved mental health outcomes and reduced rates of breast and ovarian cancer [10,11]. Although the positive impacts of EBF are recognized internationally, the Global Breastfeeding Collective’s goal of an overall EBF rate of 50% by 2025 will be hard to reach [12,13]. Globally, the most commonly documented barriers to EBF are financial constraints, time commitment, insufficient maternity protection, and a lack of breastfeeding support [14-16]. In the last decade, many countries have launched public health campaigns, such as educational awareness programs, to improve rates of EBF. Awareness programs are important but often do not take into account the financial and time constraints associated with breastfeeding and are not always adapted for mothers from lower socioeconomic communities [17-22].

Social transfer programs have been effective in improving health outcomes while also reducing socioeconomic inequalities, especially in low- and middle-income countries [23-25]. Puerto Rico launched a small-scale cash transfer program and found an increase in breastfeeding outcomes for those receiving a financial incentive [26]. In addition, a recent study conducted in Vientiane, Lao People’s Democratic Republic (LPDR), demonstrated that a social transfer program significantly improved EBF rates at 6 months postpartum [27]. Mothers who received a conditional social transfer had the highest prevalence of EBF at 6 months, followed by those who received an unconditional social transfer [27].

Brazil has one of the highest levels of economic and health inequalities globally [28]. Most of Brazil’s wealth is held by 1% of the population, demonstrating the extreme disparities faced in the country [29,30]. To reduce these prominent wealth and health gaps, Brazil implemented a national conditional cash transfer program called Bolsa Família in 2003, which provides financial incentives to families from low-income communities to help support and improve child health and education [31,32]. Although Bolsa Família has been associated with reductions in poverty and improvements in child health outcomes, disparities continue to persist. These differences are also reflected in breastfeeding practices, where low-income mothers have lower rates of EBF compared to mothers with high income [33,34]. Brazil reports an overall EBF rate of 39% for children aged below 6 months [35,36]. While EBF rates are 46% in high-income communities, they are only 33% in low-income communities [37-39]. To address this, Auxílo Nutriz was introduced within Bolsa Família, offering an additional social transfer of 50 Brazilian Reais (US $10) to support new mothers during the first 6 months postpartum. This program is still in its early stages; therefore, data on outcomes have yet to be evaluated.

### This Study

This protocol aims to implement a randomized controlled trial (RCT), the Social Transfers for Exclusive Breastfeeding in Brazil (STEBB) program in São Paulo, to assess the effectiveness of a targeted social transfer intervention in an upper-middle-income country with persistent inequities. Building upon the design of a successful program conducted in LPDR, the STEBB intervention will evaluate the impact of breastfeeding education combined with either no social transfer, an unconditional transfer, or a conditional transfer on EBF outcomes. By leveraging Brazil’s existing national social transfer program, this study will explore whether a more focused and enhanced intervention can further promote EBF. The primary outcomes of this study are the prevalence of EBF at 6 months postpartum and the overall duration of EBF. We hypothesize that mothers receiving a conditional social transfer will have the highest rates of EBF at 6 months and, on average, the longest duration of EBF, followed by those receiving an unconditional social transfer and no social transfer.

## Methods

### Overview

The STEBB study is a prospective, 3-arm RCT conducted in São Paulo, Brazil. Before implementing the intervention, we conducted a qualitative study to identify culturally relevant social transfers and ensure social acceptability of the program.

The qualitative study involved 3 focus group discussions with mothers and fathers as well as key informant interviews with 3 health care workers and 2 representatives from the Ministry of Health and the Ministry of Social Development and Fight Against Hunger. These focus group discussions and key informant interviews assessed behaviors, perceptions, and barriers related to breastfeeding as well as the feasibility of implementing a social transfer program aimed at improving EBF rates. Findings from the qualitative research informed the design of a culturally appropriate and acceptable social transfer intervention for participants in Brazil, including options such as diapers, hygiene products, children’s clothes, toys, or books.

### Recruitment

A total of 400 mother-infant dyads will be recruited at the University Hospital of São Paulo and Amparo Maternal during the postpartum hospitalization period. Recruitment will take place over 8 months, with a target of enrolling 50 dyads per month. Each dyad will be followed for a period of 2 years (Figure 1).

**Figure 1 figure1:**
[figure not shown]
Study timeline.

At baseline, mothers will be randomly assigned to one of the three groups (Figure 2): (1) control group—no intervention; (2) intervention arm 1—receipt of a social transfer at the 6-month visit; and (3) intervention arm 2—receipt of a social transfer at the 6-month visit, conditional on EBF status at the 6-month visit. All 3 groups will receive educational material on breastfeeding. The intervention is structured into 3 study arms to enable comparison between the 2 intervention groups and the control group, allowing us to evaluate the effects of conditional versus unconditional programs. Evidence from LPDR has shown that conditional social transfers significantly improved EBF rates [27]. Bolsa Família is another example of a successful conditional social transfer program for child health outcomes [34]. By contrast, our qualitative study found that participants expressed concerns about conditional programs targeting breastfeeding outcomes, particularly due to the pressure placed on mothers and the lack of reliable tools to accurately assess EBF. Given this context, we aim to evaluate both types of interventions to determine their respective impacts and assess which intervention is more effective and feasible for potential large-scale implementation.

**Figure 2 figure2:**
[figure not shown]
Study arms.

The study participants will be contacted at the hospital after giving birth. New mothers will be eligible to participate in the study if they (1) gave birth in the last 72 hours, (2) are exclusively breastfeeding at the time of recruitment and intend to continue to exclusively breastfeed, (3) are beneficiaries of the Bolsa Família program or part of the eligible population for Bolsa Família registered in the Unified Social Assistance Registry (Cadastro Único), (4) live in São Paulo, (5) have no illnesses that contraindicates breastfeeding, (6) had a healthy singleton infant of 37 weeks or more gestation with a birth weight of at least 2500 g, and (7) agree to participate and sign an informed consent form (ICF). If underage (aged between 12 and 17 years), a legal representative will also have to agree to sign the informed consent.

A team of 2 nurses will be responsible for enrollment and follow-up of participants. The nurses will explain the study to all participants and collect the written ICF. Randomization will be done using a simple random number draw generated by ODK, used to collect data on tablets. The nurses will not have access to the random allocation sequence.

### Sample Size and Power Calculation

We initially planned to only recruit mother-infant dyads at the University Hospital of São Paulo based on the documented average of 200 births per month in 2024. However, after 2 months of recruitment, we observed a lower-than-expected birth rate. To ensure timely enrollment, we expanded our recruitment to include a second recruitment center, Amparo Maternal, which reported an average of 400 births per month in 2024. As a multicenter study, we are confident in reaching our target sample size of 400 dyads by October 2025.

We plan to enroll 200 participants in the control arm and 100 participants in each of the 2 intervention arms. This sample size provides 80% power to detect an increase in EBF from an anticipated 32.5% (65/200) in the control arm to 47% (94/200) in either intervention arm.

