### Statistical Analysis

All participants enrolled in this study will be included in the analysis and will be assessed by intervention group (control, unconditional, and conditional). EBF duration will be analyzed after completion of end line visits using an adjusted Cox proportional hazards model to estimate hazard ratios and 95% CI limits. We will use an adjusted logistic regression model to assess EBF at 6 months in the intervention and control groups. A complete case analysis will be used to address missing data.

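### The power statement prints 94/200 for an intervention arm planned at 100 mothers; with 200 vs 100, power is about 68% at two-sided 5% (about 79% at one-sided 5%), not 80%

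*Protocol article*

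**What the plan says.** The relevant text is in the Protocol article, Sample Size and Power Calculation. The allocation is fixed first: "We plan to enroll 200 participants in the control arm and 100 participants in each of the 2 intervention arms". The next sentence claims that these numbers give "80% power to detect an increase in EBF from an anticipated 32.5% (65/200) in the control arm to 47% (94/200) in either intervention arm". The total agrees with the Recruitment section: "A total of 400 mother-infant dyads will be recruited at the University Hospital of São Paulo and Amparo Maternal".

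The text after Figure 1 says that the three-arm structure is there "to enable comparison between the 2 intervention groups and the control group", and goes on to say that conditional and unconditional programmes are to be judged for their separate effects.

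The power paragraph states no alpha, sidedness or test. The nearest indication is in Statistical Analysis, where EBF duration will be analysed with an "adjusted Cox proportional hazards model to estimate hazard ratios and 95% CI limits". The sentence on the logistic model for EBF at 6 months gives no interval or significance level.

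**The concern.** Two adjacent sentences disagree. The first puts 100 mothers in each intervention arm. The second attaches a denominator of 200 to one such arm. A denominator of 200 on the intervention side exists only if the two transfer arms are combined, and the sentence does not describe that comparison.

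The denominator matters because power depends on the smaller group. If 80% does not hold for 200 vs 100, the trial's only power statement overstates its ability to detect the planned effect in a single transfer arm. EBF at 6 months is a primary outcome, and the authors hope the results will inform national policy. A reader weighing an inconclusive result in one arm needs to know whether the chance of missing the planned effect was 1 in 5 or nearer 1 in 3.

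**Working it through.** **Inputs.** From Sample Size and Power Calculation: p1 = 0.325 (control), p2 = 0.47 (intervention), n1 = 200 (control), n2 = 100 (one intervention arm). Alpha and sidedness are not stated, so both two-sided 5% (z = 1.960) and one-sided 5% (z = 1.645) are tried.

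**Fractions.** 65/200 = 32.5% fits the control arm. 94/200 = 47%, but an arm of 100 would give 47/100. 94/200 fits only 100 + 100 mothers.

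**Formula.** Unadjusted two-proportion z-test with pooled variance under the null:

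- p̄ = (n1·p1 + n2·p2)/(n1 + n2)
- SE0 = √[p̄(1 − p̄)(1/n1 + 1/n2)]
- SE1 = √[p1(1 − p1)/n1 + p2(1 − p2)/n2]
- power = Φ[(p2 − p1 − z·SE0)/SE1]

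**Planned arms, 200 vs 100.** p̄ = (65 + 47)/300 = 0.3733; SE0 = 0.05924; SE1 = 0.05990; difference = 0.145.

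- Two-sided 5%: (0.145 − 1.960 × 0.05924)/0.05990 = 0.482, so power = 68.5%.
- One-sided 5%: (0.145 − 1.645 × 0.05924)/0.05990 = 0.794, so power = 78.6%.

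**Printed denominator, 200 vs 200.** p̄ = (65 + 94)/400 = 0.3975; SE0 = 0.04894; SE1 = 0.04840.

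- Two-sided 5%: (0.145 − 1.960 × 0.04894)/0.04840 = 1.014, so power = 84.5%.
- One-sided 5%: 90.9%.

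**Can the stated 80% be reproduced?**

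| Setting | Power |
|---|---|
| 200 vs 100, two-sided 5% | 68.5% |
| 200 vs 100, one-sided 5% | 78.6% |
| 200 vs 200, two-sided 5% | 84.5% |
| 200 vs 200, two-sided 5%, continuity-corrected | 81.9% |
| 180 vs 180 (assumed 10% loss), two-sided 5% | 80.5% |

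Three settings come within 2 points of 80%. Each needs an ingredient that the article does not mention: a one-sided test, a continuity correction, or a loss allowance.

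**Sensitivity to method, 200 vs 100, two-sided 5%.** Unpooled variance 67.8%, arcsine 68.1%, exact power of the chi-square test 68.6%, continuity-corrected 64.0%. None approaches 80%.

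**Rate detectable with 80% power, 200 vs 100.** Solving the formula for p2 gives about 49.2% at two-sided 5% and about 47.3% at one-sided 5%. To keep 47% with 80% power at two-sided 5% and the same 2:1 ratio would take about 264 control and 132 per intervention arm.

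**The case against.** The strongest defence is a one-sided test. The article speaks of detecting an increase and states a directional hypothesis, and at one-sided 5% the planned 200 vs 100 gives 78.6%, which could have been rounded to 80%. The 95% interval in Statistical Analysis is written for the Cox model, not for the prevalence comparison, so it only hints at a two-sided level for this calculation. This stands to the extent that 68% cannot be stated without its two-sided 5% condition. It does not rescue the paragraph: no one-sided test is declared anywhere, 78.6% is still short of 80%, and 94/200 remains wrong for one arm.

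A reader might infer that the 80% was computed with 200 mothers per intervention arm. The documents do not support that. Plain 200 vs 200 gives 84.5%, and the fraction may be no more than a misprinted way of showing 47%.

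A reader might also add that the calculation makes no allowance for loss although "A complete case analysis will be used to address missing data". A journal article commonly leaves such an allowance to the full protocol, so its absence is not counted here. The 10% loss in the table above is only one conceivable route to 80%.

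Finally, the planned analysis is an adjusted logistic model, whose power can differ from that of an unadjusted comparison. That is fair, but the article describes its power only through two raw proportions, and the check is made on those terms.

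**Conclusion.** The point holds as an internal contradiction plus a power figure that the stated design does not deliver under the conventional assumption. The contradiction needs no assumption: 200 is not the size of either intervention arm.

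The size of the shortfall depends on an alpha that the article does not give. At two-sided 5%, per-arm power is about 68%, so the chance of missing a true 47% is about 32% rather than 20%. At one-sided 5% it is about 79%, and the shortfall is trivial. Both figures assume an unadjusted two-proportion test, 32.5% in control, and outcome data on all 400 mothers. The origin of the 80% is undetermined, and nothing here depends on knowing it.

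**What to change.** In Sample Size and Power Calculation:

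1. Correct 94/200 to 47/100. If the figure was meant for both transfer arms pooled against control, say so and remove the reference to a single intervention arm.
2. State the alpha, the sidedness and the test behind the power figure.
3. If two-sided 5% applies, restate per-arm power for 32.5% vs 47% as about 68%, or give about 49% as the intervention rate detectable with 80% power. If one-sided 5% was intended, say so and give about 79%.

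The cost is wording only, with no change to enrolment or allocation. Under two-sided 5% the stated power becomes less favourable. The Results section puts completion of the primary outcome at May 2026, so the correction should be on record before those data are analysed.

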### Study Design

This study includes 5 visits: at birth (baseline), 1 month, 6 months (end line), 1 year, and 2 years (Figure 3). At baseline, the participants will complete a short questionnaire, and biological samples will be collected from both the mother and infant. At the end of the visit, the nurse will provide detailed information on the intervention depending on the group the mothers are randomly assigned to. If the mothers are assigned to an intervention group, they will be given a gift catalog to choose a social transfer for the visit at 6 months. The catalog will offer gift packages ranging from baby clothes, hygiene products, transportation vouchers, and developmental toys for the child. All 3 groups will receive educational pamphlets explaining the benefits of breastfeeding and providing breastfeeding guidelines.

During the follow-up visits (at 1 month, 6 months, 1 year, and 2 years), data collection will include a questionnaire and biological samples from both the mother and infant. The intervention groups (unconditional and conditional) will receive a social transfer at the 6-month visit. For mothers in the conditional group, assessors will review the maternal feeding reports as well as visually verify milk expression during biological collection.

**Figure 3 figure3:**
[figure not shown]
Study visits and data collection.

### Data Collection Tools

STEBB provides a questionnaire at each visit.

#### Baseline: At Birth

The baseline questionnaire is given to the mothers during postpartum hospitalization. The questionnaire will consist of the inclusion criteria and basic demographic questions, such as education, employment, and marital status. We will also extract anthropometric measurement data from the child (weight, length, mid and upper arm circumference, abdominal circumference, chest circumference, and head circumference) and mother (blood pressure, height, weight, and heart rate) through medical records. Hemoglobin levels of the mother and infant will be collected and measured using the HemoCue Hb 301. Infant feces and human milk samples will also be collected.

#### Follow-Up: 1 Month Postpartum

The 1-month questionnaire is given to the mothers at 1 month postpartum during a hospital follow-up visit. The questionnaire includes maternal medical and obstetric history; child health (infectious and chronic illnesses, hospital visits, medication, vitamins, and vaccinations); anthropometric measurements from mother (height and weight) and child (weight, length, mid and upper arm circumference, abdominal circumference, chest circumference, and head circumference); breastfeeding and infant feeding; Resilience Scale-14 [40]; Breastfeeding Self-Efficacy Scale–short form [41]; Perceived Maternal Parenting Self-Efficacy Scale [42]; Iowa Infant Feeding Attitude Scale [43]; Postpartum Specific Anxiety Scale [44]; Edinburgh Postnatal Depression Scale [45]; Growth, Resilience, Integrity, and Tenacity Scale–short form [46]; household assets; family and gender roles; and maternal intimacy and behavioral measurements (diet, tobacco use, and alcohol consumption). This information will be collected during the 1-month visit. Mother and infant hemoglobin levels, along with infant feces and milk samples, will also be collected.

#### End line: 6 Months Postpartum

The end line questionnaire is given to the mothers at approximately 6 months (1 week earlier or later) postpartum during an at-home visit. The questionnaire includes child health (as done at 1 month), maternal and child anthropometric measurements (as done at 1 month), breastfeeding and infant feeding, Big Five Personality Scale [47], Iowa Infant Feeding Attitude Scale, Perceived Stress Scale [48], Postpartum Specific Anxiety Scale, Edinburgh Postnatal Depression Scale, Caregiver Reported Early Development Instruments–short form [49], and maternal intimacy and behavioral measurements (diet, tobacco use, and alcohol consumption). Mother and infant hemoglobin levels, along with infant feces and human milk samples, are also collected.

